### Data collection

All data collected will be recorded using unique participant identifiers (IDs) to anonymize collected information. The effectiveness outcome measures are based on self-report and they will be collected at baseline and 12-week and 24-week assessment visits. They will be completed with assistance from a research coordinator blinded to participant allocation. Implementation evaluation outcomes (collected pre- and postprogram from clinic staff and SSM teachers, and postintervention from SSM participants) will be completed by a study staff. Qualitative implementation measures will be audio-recorded, transcribed verbatim, and anonymized. The final dataset will be accessible by all study investigators.

### Privacy, confidentiality and security

All questionnaires and forms will be completed digitally using REDCap and stored on a secure server based at LTRI. Following completion of a data transfer agreement, data in paper format (questionnaires) will be transported in a locked briefcase from the clinic to LTRI and will be stored in a locked cabinet for the duration of the study and discarded via secure shredding after a period of 7 years. All data will be coded with unique participant IDs to protect patient confidentiality, and documents linking participants to their IDs will be stored on a secure database at LTRI for the duration of the study. The code key with identifying data will only be accessible to research coordinators responsible for recruitment, assessment and scheduling, unless a participant’s health is at risk and unblinding is required due to extenuating circumstances. All the focus groups and interviews will be audio-recorded and transcribed verbatim. The transcripts will be read against the audio-recordings to remove identifiable information and to check for accuracy. All audio files and electronic copies of the transcripts will be transported on encrypted USB drives or audio-recording devices in a locked briefcase to LTRI and stored on the secure server for the duration of the study. Any hard copies of the transcripts will be stored at LTRI in a locked cabinet. After a period of 7 years all digital files will be permanently deleted, and hard copies will be discarded via secure shredding. The consent form informs participants that the research team and research ethics boards will have access to study data where relevant, and that they may withdraw from the study and request to have their study information removed at any time. No biological specimens will be collected.

### Data analysis

#### Effectiveness

The primary and secondary outcomes (PHQ-9 score, Brief Pain Inventory, opioid equivalent dose, and 36-item Short From survey) will be measured at baseline and at 12 and 24 weeks. We will examine the distribution of primary and secondary outcomes for normality. If required, appropriate transformation (for example Box–Cox transformation) will be applied to correct the possible non-normality. Our primary and secondary outcomes are continuous and measured over three time points. We will use a longitudinal data analysis approach to asses within-group changes (change over time within each arm) and between-group changes (difference between two groups at each time point) while these assessments are adjusted for potential confounders (such as age, gender, ethnicity and employment status) and the correlation among the repeated measures. We will use a generalized estimation equation method with AR(1) (autoregressive) covariance structure or the random effect method to adjust for the correlation among the repeated measures of the participants. The longitudinal analysis also allows us to compare the change from the baseline at 12 and 24 weeks between intervention and control groups (difference in differences). The analysis will follow the intention-to-treat principle; all participants who are randomized will be included in the analyses and analyzed in the arms to which they were assigned. We will first analyze the data using observed data (complete case), then we impute the missing observations and obtain multiply imputed estimates. There are no prespecified subgroup analyses.

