***Inclusion criteria***	
1. >45 years of age; chronic pain (pain ≥3 months duration in any body region by self-report)	Older people with chronic pain are disproportionately affected by harms from prescribed opioids such as overdose and death [36]
2. On LTOT (any opioid at any dose for ≥3 months by self-report)	Known contribution of LTOT to depression and secondary outcome of reducing opioid use/dose [13]
3. Comorbid depressive symptoms of mild to moderate severity (PHQ-9 score 10–19)	People with subsyndromal depressive symptoms (PHQ-9 score 5–9) are less likely to show an effect from any intervention
4. Understanding of English language; able to sit for 20–25 min without significant discomfort; be willing and able to attend all four training sessions of SSM/HEP, as well as 75% of follow-up sessions	Ensure ability to participate in interventions which will be delivered in English only and mostly in a seated position

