Primary: change in nine-item Patient Health Questionnaire (PHQ-9) scores from baseline to 12-week follow-up and 24-week follow-up (continuous)	The PHQ-9 is a well-validated and widely used self-report scale used in depression and chronic pain clinical care and research. Reduction in a continuous outcome score is a more sensitive test than percent reduction in scores that have been reported in some depression studies [5, 45, 46]. A self-report scale is more feasible than an assessor-rated scale (e.g., Hamilton Depression Rating Scale (HAM-D17)) given the site characteristics
Secondary A: change in Brief Pain Inventory (BPI) from baseline to 12-week follow-up and 24-week follow-up (continuous)	The BPI is a validated self-report scale used in pain trials and clinical pain practice and is a core outcome measure per the IMMPACT recommendations [47]. Two independent measures are included—pain severity and pain interference with function—and both are clinically relevant outcomes
Secondary B: change in opioid dosage (reported in total daily morphine equivalents) from baseline to 12-week follow-up and 24-week follow-up (self-reported; continuous measurement with conversion to total daily morphine equivalents using standardized conversion tables)	Self-report of opioid dose via patient log is the most common measure of opioid use in clinical research trials [48]. Given that patients are on a variety of distinct opioids and that some patients may be on >1 formulation, there is a need for common reporting as provided by morphine equivalent doses
Secondary C: change in health-related quality of life (QoL; by the 36-item Short Form survey (SF-36)) from baseline to 12-week follow-up and 24-week follow-up (continuous measurement)	The SF-36 has been validated as a quality QoL measure in the chronic pain population and is recommended by IMMPACT [49]. It is included here as a secondary outcome with expected positive findings from pilot data collected in other meditation interventions, which demonstrate moderate-to-large effect sizes [50]. This measure is well-aligned to the intervention which is designed as a means of improving overall QoL more than as a disease treatment

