#### Sample size calculation

A practice audit at the pain clinic in which the study will be conducted identified a high degree of comorbid depression and chronic pain in a random selection of 50 patients. Mean PHQ-9 score was 11 (standard deviation 5.7), where scores ≥10 indicate clinical depression. Sixty percent of patients had PHQ-9 scores ≥10 but only 4% had scores ≥20 (severe depression). This audit also identified three pools of patients from which subject participants can be recruited. These include: 1) new consults (30/week of which 38% meet inclusion criteria; *n* = 720 over an estimated 6-month recruitment period); 2) current patients on LTOT prescribed by physicians outside the clinic (*n* = 212); and 3) current patients on LTOT prescribed by clinic physicians (*n* = 194). The estimated total pool of eligible patients to recruit from over a 6-month period is thus about 1100.

In terms of estimated sample size, the primary outcome is continuous as measured by PHQ-9. The standard deviation of the PHQ-9 is 5 units and we anticipate a 2.5-unit difference at the end of the study between the intervention and control groups based on extrapolation of the pilot data [51]. This study is a two-arm RCT; therefore, we used a two-sample *t* test to calculate the sample size to have at least 80% power to detect differences in PHQ-9 scores of 2.5 or larger at 5% type 1 error. The resulting estimated sample size is 64 participants in each arm. We inflated the sample size by 25% to account for dropouts, which is reasonable given an attrition rate of 13% seen in the pilot study [36]. Therefore, we will recruit and randomize a total of 160 participants, with 80 participants in each arm.

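### A look at the outcomes' own distributions can move the primary PHQ-9 analysis off the scale on which the trial was powered

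*Protocol article*

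**What the plan says.** In the protocol article, under Data analysis, Effectiveness, the first analytic step is "We will examine the distribution of primary and secondary outcomes for normality". The next is "If required, appropriate transformation (for example Box–Cox transformation) will be applied to correct the possible non-normality". The variables listed there are the PHQ-9, BPI and SF-36 scores and the opioid dose, each at baseline, 12 and 24 weeks. They go into a longitudinal model (GEE with AR(1), or random effects), and the change from baseline is compared between arms as a difference in differences.

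Three other places bear on this:
- Table 1 limits entry to PHQ-9 scores of 10–19 and requires every participant to be on an opioid.
- Table 2 defines each outcome as a change, for example "change in opioid dosage (reported in total daily morphine equivalents) from baseline to 12-week follow-up and 24-week follow-up".
- The sample size section seeks "power to detect differences in PHQ-9 scores of 2.5 or larger", taking a standard deviation of 5 PHQ-9 units.

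**The concern.** The rule has three weaknesses as worded.

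1. **The trigger is misplaced.** Normality assumptions, where they matter at all, concern the residuals of the model. The rule looks at the outcomes as measured, and baseline is one of the three time points listed. Baseline PHQ-9 is an integer cut at both ends by eligibility, so it cannot look normal.
2. **The scale of the primary effect is left to the data.** The trial is powered on raw PHQ-9 points. Once scores are transformed, the treatment contrast is in other units.
3. **The choice is made late.** The transform, and any constant added to cope with scores of 0 (or with negative values, if change scores are transformed), would be picked after the outcome data have been seen.

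At stake is whether the primary result can be compared with the 2.5-point target, and whether its scale was fixed in advance.

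**Working it through.** **The plan's own figure.** Difference 2.5, SD 5, 80% power, 5% type I error (two-sided assumed). The normal approximation gives n = 2 × (1.960 + 0.842)² × 5² / 2.5² = 62.8, so 63 per arm. The exact t-test solution is 63.77, so 64 per arm, with power 80.1% at 64. The stated 64 is reproduced, and it rests wholly on the raw PHQ-9 scale.

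**Baseline shape.** Inputs: the practice audit (mean 11, SD 5.7) and the entry window 10–19. A normal shape for the audit scores is assumed. Rounding to integers and truncating to 10–19 gives mean 13.7, SD 2.67, skewness 0.33 and excess kurtosis −0.97. In simulated samples of 160, Shapiro–Wilk at the 5% level rejected normality in essentially 100%. After Box–Cox it still rejected in essentially 100%, because a power transform does not undo truncation.

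**Is normality needed?** Simulated PHQ-9 at follow-up: SD 5, rounded, bounded at 0–27, 64 per arm, assumed control mean 6 to 9. The untransformed t test had type I error of 4.8% to 5.2%. Power for a 2.5-point shift applied before bounding was 77% to 79%, slightly below 80.1%; bounding at 0 shrinks the observed difference a little.

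**Zeros at follow-up.** P(score 0) = Φ((0.5 − mean)/5).
- Assumed mean 6: Φ(−1.1) = 13.6%. Chance of at least one zero among 64: 1 − (1 − 0.136)⁶⁴, about 99.99%.
- Assumed mean 11.5: Φ(−2.2) = 1.4%. Chance of at least one zero among 64: about 59%.

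Standard Box–Cox software refuses zeros and negatives. A shift (y + 1) or Yeo–Johnson runs on such data, but someone must choose it.

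**Negative values, only if change scores are transformed.** P(change < 0) = Φ((−0.5 − mean change)/5). Assumed mean changes of −1 to −5 give 54% to 82%.

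**What a transformed contrast means.** On log(y + 1), a fall from 14 to 11.5 is ln(15/12.5) = 0.18, and a fall from 5 to 2.5 is ln(6/3.5) = 0.54. Both are 2.5 PHQ-9 points, yet the second counts about three times as much. (The starting scores are illustrative.)

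**Effect on the verdict.** Simulated trials with 64 per arm, baseline from the 10–19 window, follow-up SD 5, difference 2.5, assumed correlation 0.4, and control mean 8 or 10 at follow-up. Compared with the analysis of raw change, significance at 5% flipped in about 0.4–3% of trials with a shifted Box–Cox and in about 10–12% with log(y + 1).

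**The case against.** The strongest reply is that the rule is conditional and Box–Cox is only an example. A transform that cannot take the data would not be an appropriate one, so a shifted version, another transform or none at all are within the wording. That is correct. A reader might infer that the plan commits to Box–Cox and that remitted or improving participants would have no analysable value. The documents do not support this. A score of 0 is undefined only for a Box–Cox parameter of 0 or below, and a shift removes the problem. Negative values arise only if change scores are transformed, whereas the analysis section models the scores and derives change from the model. Opioid dose cannot be 0 at entry.

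A reader might also infer that the check is bound to fire. The article names no formal test. An analyst looking at skewness of 0.33 could decide that nothing is required, and the 10–19 window does not apply at 12 weeks. So the 100% figure describes what a formal test at baseline would do, not what the plan prescribes.

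Finally, the shift constant, the back-transformation and the exact trigger are details that an article may leave to an analysis plan. Their absence is not the point here. What stands is the rule that is written: it bases the decision on the outcome's own distribution and lets that decision change the scale of the primary analysis.

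**Conclusion.** The point holds in this limited form. The article allows a data-driven transformation of the primary outcome, triggered by a feature the planned methods do not need, and the resulting contrast could not be read against the 2.5-point difference on which the trial was sized. For baseline PHQ-9 the trigger partly reflects the eligibility window, and Box–Cox does not repair that.

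The statistical harm is modest: a changed verdict in about 0.4–3% of simulated trials with a shifted Box–Cox and about 10–12% with log(y + 1). Those figures assume a correlation of 0.4, SD 5 and control means of 8 or 10, none of which except the SD comes from the article. The larger cost is to interpretability and prespecification. A blanket ban on transforming opioid dose does not follow, since skew and follow-up zeros are plausible there and transformation is one defensible choice.

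**What to change.** State that the primary PHQ-9 analysis is done on the original scale whatever the distribution, with robust (sandwich) or bootstrap confidence intervals, and that model checks are made on residuals. Limit any transformation or rank-based method for the PHQ-9 to prespecified sensitivity analyses. For opioid dose, name in advance any transformation to be used and make sure it can handle zeros.

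The cost is a few sentences of wording and slightly more analysis work. The sample size is unaffected.

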***Exclusion criteria***	
1. Psychiatric conditions other than depression, including substance use disorder, psychosis and cognitive impairment as established by the MINI; severe depression (PHQ-9 ≥20) and risk of imminent suicide as per MINI and PHQ-9; noncorrectable, clinically significant sensory impairment; acutely unstable physical illnesses, including delirium or acute cerebrovascular or cardiovascular events within the last 6 months; a terminal medical diagnosis with prognosis of less than 12 months	People with these attributes are theoretically less likely to benefit from the group meditation intervention and/or HEP control condition. People with severe depression (i.e., PHQ-9 ≥20) may need a standard intervention (e.g., psychotherapy, antidepressant medications). In certain cases, a patient’s symptoms may worsen (e.g., patients with psychosis) or the patient may be too frail to complete the study (e.g., medically unstable patients) [37]
2. Currently practicing any form of mind–body intervention	To limit confounding variables
3. Inability to provide informed consent	As per ethical norms for research involving human subjects

*Abbreviations: HEP* Health Enhancement Program, *LTOT* Long-term opioid therapy, *MINI* Mini-International Neuropsychiatric Interview, *PHQ-9* Patient Health Questionnaire, *SSM* Sahaj Samadhi Meditation

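### Baseline PHQ-9 should be a covariate in the primary model: neither stated contrast is more precise, and one permitted fit can understate the 12-week standard error

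*Protocol article*

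**What the plan says.** Under Data analysis – Effectiveness, the outcomes, baseline included, are analysed over three time points. Correlation within participants is to be handled by a "generalized estimation equation method with AR(1) (autoregressive) covariance structure or the random effect method". Two between-group contrasts are described: the group difference at each time point, and a model that can "compare the change from the baseline at 12 and 24 weeks between intervention and control groups (difference in differences"). The assessments are to be "adjusted for potential confounders (such as age, gender, ethnicity and employment status"), an open list that does not name baseline PHQ-9. The type of standard error is not stated, nor whether variances may differ between visits.

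Table 1 limits entry to "Comorbid depressive symptoms of mild to moderate severity (PHQ-9 score 10–19") and excludes "severe depression (PHQ-9 ≥20) and risk of imminent suicide as per MINI and PHQ-9". The sample size section reports a clinic audit: "Mean PHQ-9 score was 11 (standard deviation 5.7), where scores ≥10 indicate clinical depression". For planning it states: "The standard deviation of the PHQ-9 is 5 units and we anticipate a 2.5-unit difference at the end of the study".

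**The concern.** There are two separate issues.

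**Precision.** The plain week-12 difference takes no account of a participant's starting score, and the difference in differences subtracts all of it. In regression terms they fix the coefficient on baseline at 0 and at 1. Baseline adjustment estimates that coefficient, so its residual variance cannot exceed either. The trial is planned at almost exactly 80% power, so a gain that needs no extra data is worth having.

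**Error rate under one permitted fit.** In their usual forms, AR(1) and a random intercept assume the same variance at every visit. Eligibility compresses PHQ-9 at entry, while follow-up scores are unrestricted. If the model pools variance over visits and uses model-based standard errors, the compressed baseline pulls the pooled variance below the week-12 variance. The plain week-12 difference then looks more certain than it is.

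**Working it through.** **The plan's own figure.** Two-sample t test, difference 2.5, SD 5, two-sided 5%: 63 per arm gives 79.5% power and 64 per arm gives 80.1%. Then 64 × 1.25 = 80 per arm, 160 in total. The stated sample size reproduces.

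**Inputs.** From the article: audit mean 11 and SD 5.7, entry range 10–19, 64 analysed per arm, difference 2.5. Assumed: an approximately normal score before restriction; the screening score is the baseline score; an unrestricted SD of 5.7 at follow-up too, equal at 12 and 24 weeks; and an underlying (unrestricted) correlation r of 0.4–0.8 between baseline and follow-up.

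**Step 1, baseline spread.** A normal distribution with mean 11 and SD 5.7, discretised to whole scores and cut to 10–19, has mean 13.7 and SD 2.67, so its variance is V0 = 7.13.

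**Step 2, variance per participant for each contrast.**
- Baseline-adjusted: A = 5.7²(1 − r²)
- Plain 12-week difference: P = r²·V0 + A
- Change from baseline: C = (1 − r)²·V0 + A

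At r = 0.5: A = 32.49 × 0.75 = 24.37; P = 0.25 × 7.13 + 24.37 = 26.15; C is the same. The reduction is 1 − 24.37/26.15 = 6.8%.

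| r | A | P | C | Cut against P | Cut against C |
|---|---|---|---|---|---|
| 0.4 | 27.29 | 28.43 | 29.86 | 4.0% | 8.6% |
| 0.5 | 24.37 | 26.15 | 26.15 | 6.8% | 6.8% |
| 0.8 | 11.70 | 16.26 | 11.98 | 28.1% | 2.4% |

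Against the better of the two contrasts, the gain is therefore about 2–7%. At r = 0.5, power with 64 per arm goes from 78.4% to 81.1%.

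**Step 3, the same question on another scale.** Take baseline SD 2.7, 12-week SD 5, and the correlation as observed after restriction. The variance penalty of difference in differences against baseline adjustment is 12%, 6%, 2% and 0% at observed correlations 0.2, 0.3, 0.4 and 0.5. At 0.2, power is about 78% against 82%; at 0.5 it is about 90% for both. The two scales agree: an underlying r of 0.5 is an observed correlation of 0.5 × 2.67/5.11 = 0.26.

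**Step 4, plain 12-week difference with a constant-variance random intercept and model-based standard error.** The pooled variance is (V0 + 2P)/3, and the ratio of reported to true standard error is √(pooled/P).
- r = 0.5: (7.13 + 52.30)/3 = 19.81; √(19.81/26.15) = 0.870; type I error 2Φ(−1.96 × 0.870) = 8.8%.
- r = 0.4: 9.0%. r = 0.8: 7.7%.
- With SD 2.7 at baseline and 5 at follow-up: ratio 0.874, type I error 8.7%. With SD 5 throughout: ratio 1.00, type I error 5%.

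For this contrast, the entry restriction is the cause.

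**Step 5, difference in differences.** Assumed observed correlations are 0.2–0.5 (baseline to 12 weeks) and 0.5–0.8 (12 to 24 weeks). The random-intercept model-based standard error is 0.89–1.07 of the true value with the restricted baseline and 0.87–1.02 with baseline SD 5. For model-based AR(1) the ranges are 0.76–1.01 and 0.79–1.00. The error is much the same either way, so it comes mainly from the correlation pattern.

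**Step 6, robust standard errors.** In three simulated scenarios (64 per arm, 1,000 runs each), the null rejection rate for difference in differences was 5.3–5.6% for GEE-AR(1) with sandwich standard errors. It was 9.7–16% for GEE-AR(1) with model-based standard errors and 6.1–8.7% for the random intercept.

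**The case against.** GEE is the first method named. With its usual sandwich standard error, AR(1) is only a working structure and need not be right; Step 6 bears this out. A random-effect model can also carry visit-specific variances, and the article does not rule that out. The choice of standard error is detail that a journal article may leave to the full plan. All of this stands, and it limits the error-rate point to one possible fit.

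The covariate list is illustrative, so baseline PHQ-9 is not excluded. That is fair. But the model already carries baseline as an outcome, and adding it as a covariate would make a different model from the one described.

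The precision gain is modest, and the entry restriction makes it smaller. With an unrestricted baseline SD of 5, difference in differences would cost 33–67% in variance, against 0–12% here. The 28% at the top of the range is against the plain difference at r = 0.8, where the change contrast loses only about 2%. This stands too, and it is why the gain against the better contrast is the fair summary.

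The screening and baseline scores may be separate measurements; the schedule and flow figures are not available. A fresh baseline measure would weaken the restriction.

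**Conclusion.** The point holds as a recommended improvement. Baseline adjustment is at least as precise as either stated contrast throughout the range examined. It cuts variance by about 2–7% against the better one, worth roughly three points of power at r = 0.5. The type I error of about 8–9% is conditional. It applies to the plain 12-week difference if the random-effect option is fitted as a constant-variance random intercept with model-based standard errors.

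A reader might infer that the plan will give wrong error bars because eligibility restricts the baseline. The article does not support that. It does not commit to model-based standard errors, GEE with robust ones keeps the error rate, and the model-based error in the difference in differences is present without the restriction. The sample size is unaffected.

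The size of every figure rests on the assumed correlations, a normal shape, the assumed follow-up SD, and a screening score that serves as the baseline score.

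**What to change.** State one primary model: PHQ-9 at 12 and 24 weeks as outcome, baseline PHQ-9 as covariate, arm, visit and arm-by-visit terms, and an unstructured visit covariance or robust standard errors. An equivalent choice is a three-visit model with the arms' baseline means constrained to be equal and an unstructured covariance. Name the adjusted arm difference at week 12 as the primary estimate.

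Adjusting BPI, opioid dose and SF-36 for their own baselines is sensible on precision grounds only. Eligibility sets no score or dose range on them, so the truncation argument does not carry over.

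The cost is analysis wording. Baseline PHQ-9 is already collected, and an unstructured covariance over three visits has six parameters.
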